**General plan**

**1.1 Objectives**

Primary

Is it safe and tolerable to immunize with seven or eleven DNA plasmids carrying HIV-1 genes with electroporation?

Secondary

1. Is it possible to increase immunogenicity of a DNA vaccine delivered intradermally and to reduce the number of injections needed by using electroporation?
2. Will electroporation improve/alter the quality of the immune responses induced by the HIV-1 DNA plasmids?
3. Is it possible to obtain similar immune reactivity by replacing two intramuscular boosts using MVA with two intradermal injections of HIV-1 DNA plasmids together with electroporation?
4. Can electroporation increase immunogenitcity of all included DNA plasmids to permit mixing of all vaccine plasmids instead of delivering them as two different entities?
5. Will additional DNA plasmids broaden the immune response?

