**1.2 Design**

The trial is randomised and placebo controlled.

Study Design

| **Group** | **N** | **Mode of Immunization**  **(w 0, 6 , 12)** | **Mode of delivery** | **Left arm (Ampoules 1**  **env)** | | **Right arm (Ampoules 2**  **gag, Rtmut)** | **Boost immunization**  **(w 36 and 60)** |
| --- | --- | --- | --- | --- | --- | --- | --- |
| B1 | 10 | Id  ZetaJet® | No electroporation | 1 inj 100µl  0,3 mg DNA* | 1 inj100µl  0,3 mg DNA* | | 1 im inj needle  MVA 108 pfu |
|  | 2 | Id  ZetaJet® | No electroporation | 1 inj 100µl saline | 1 inj 100µl saline | | 1 im inj needle  100µl saline |
| B2 | 10 | Id  ZetaJet® | electroporation | 1 inj 100µl  0,3 mg DNA* | 1 inj 100µl  0,3 mg DNA* | | 1 im inj needle  MVA 108 pfu |
|  | 2 | Id  ZetaJet® | electroporation | 1 inj 100µl saline | 1 inj 100µl saline | | 1 im inj needle  100µl saline |
| B3 | 10 | Id  ZetaJet® | electroporation | 1 inj 100µl  0,3 mg DNA* | 1 inj 100µl  0,3 mg DNA* | | 2 id inj Zetajet®,  tot. 0,6 mg DNA + electroporation |
|  | 2 | Id  ZetaJet® | electroporation | 1 inj100µl saline | 1 inj100µl saline | | 2 id inj Zetajet®,  tot 200µl saline +  electroporation |
| B4 | 10 | Id  ZetaJet® | electroporation | 1 inj100µl  0,3 mg DNA** mixed ampoules | 1 inj100µl  0,3 mg DNA** mixed ampoules | | 1 im inj needle  MVA 108 pfu |
|  | 2 | Id  ZetaJet® | electroporation | 1 inj100µl saline | 1 inj100µl saline | | 1 im inj needle  100µl saline |

*) 7 DNA plasmids **) 11 DNA plasmids.

Immunizations will be given as prime injections (HIV DNA) at weeks 0, 6 and 12 and as boost injections (MVA) at week 36 and week 60.

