Group B4 will be compared to groups B1-B3 to show if priming with additional HIV-related plasmids will increase immunogenicity to any of the included antigens.

###

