| B2 | 10 | Id  ZetaJet® | electroporation | 1 inj 100µl  0,3 mg DNA* | 1 inj 100µl  0,3 mg DNA* | | 1 im inj needle  MVA 108 pfu |
|  | 2 | Id  ZetaJet® | electroporation | 1 inj 100µl saline | 1 inj 100µl saline | | 1 im inj needle  100µl saline |
| B3 | 10 | Id  ZetaJet® | electroporation | 1 inj 100µl  0,3 mg DNA* | 1 inj 100µl  0,3 mg DNA* | | 2 id inj Zetajet®,  tot. 0,6 mg DNA + electroporation |
|  | 2 | Id  ZetaJet® | electroporation | 1 inj100µl saline | 1 inj100µl saline | | 2 id inj Zetajet®,  tot 200µl saline +  electroporation |
| B4 | 10 | Id  ZetaJet® | electroporation | 1 inj100µl  0,3 mg DNA** mixed ampoules | 1 inj100µl  0,3 mg DNA** mixed ampoules | | 1 im inj needle  MVA 108 pfu |
|  | 2 | Id  ZetaJet® | electroporation | 1 inj100µl saline | 1 inj100µl saline | | 1 im inj needle  100µl saline |

*) 7 DNA plasmids **) 11 DNA plasmids.

Immunizations will be given as prime injections (HIV DNA) at weeks 0, 6 and 12 and as boost injections (MVA) at week 36 and week 60.

*2.4.2 Injections*

All **DNA** immunizations will be performed with a needle-free device, ZetaJet®, according to the manufacturer’s (Bioject Inc, Portland, Oregon) instruction.

Intradermal injections will be given over the deltoid muscle. Ampoule 1 will be given in the left arm and ampoule 2 in the right arm, except in the Group B4 where a mixture of vaccines from two identical ampoules will be given in both arms. Immediately after the injection subjects randomized to Groups B2, B3 and B4 will receive intradermal electroporation over the injection sites with the CytoPulse device, DermaVax, according to the manufacturer’s instruction.

All **MVA** injections will be performed with needle and syringe in the left deltoid muscle.

The site will be inspected after the immunisation, and any local reactions recorded on the case record form.

The immunisations will take place in an outpatient setting. Participants will be closely observed for 30 minutes after each immunisation, at which point vital signs (pulse, blood pressure and respiratory rate) will be recorded on the case record form, as well as any local or systemic reaction.

The needles, syringes and other materials will be disposed of according to local hospital regulations.

As with any parenteral vaccine, epinephrine and corticosteroids must be available for immediate use if an immediate hypersensitivity reaction, such as anaphylaxis, occur. Intravenous injections of vaccines will NOT be performed.

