**8.2 Analysis**

All safety end-points will be graded by the Clinical Investigator and reviewed by the Trial Management Group. Any queries about grade and relationship to study product that cannot be resolved will be referred to the Trial Coordinating Committee for a final decision.

The primary end-points:

1. The safety of immunization with the seven or eleven DNA plasmids carrying HIV-1 genes will be assessed by clinical signs and standard biochemical and haematological laboratory tests where any worsening of the severity grade will be considered for causality with the vaccine.
2. The immunization will be evaluated by assessing local (pain, cutaneous reactions including induration), general (fever, chills, headache, nausea, vomiting, malaise, myalgia) and other unsolicited adverse events within 7 and 28 days. Any grade 3 or 4 event will be taken as an indication that the arm is less tolerable.

The secondary endpoints

The secondary endpoint (immunogenicity) will primarily be assessed by IFN-γ ELISpot 2 weeks after the third DNA immunization, the fourth DNA or first MVA immunization and after the fifth DNA or second MVA immunization. Both number of responders and magnitude of responses will be tested for significance. Additional studies will be performed at other time points using other assays such as intracellular cytokine staining, lymphoproliferation assays, epitope mapping, binding (and if indicated) neutralization antibody assays.

Group B1 will be compared with the id only group in the HIVIS study (Group A in HIVIS trial) for evaluation of the lower dose of HIV DNA (0.6 vs 1.0 mg).

Group B2 will be compared with Group B1 for evaluation of the lower dose of HIV DNA with and without electroporation.

Group B3 will be compared to the group B2 for the evaluation of HIV DNA as a boost compared to boosting with HIV MVA.

Group B4 is will be compared to groups B1-B3 to show if priming with additional HIV-related plasmids will increase immunogenicity to any of the included antigens.

Figures/tables will be prepared including all participants’ results.

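### The added-plasmid question is answered by comparing B4 with B1-B3, although only B2 shares B4's electroporation and MVA boost, so an effect of either can be read as a plasmid effect on shared antigens

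*Protocol*

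**What the plan says.** Secondary objective 5 in section 1.1 asks: "Will additional DNA plasmids broaden the immune response". Two places fix the comparison that bears on it. Section 1.5.2 reads "Group B4 will be compared to groups B1-B3 to show if priming with additional HIV-related plasmids will increase immunogenicity to any of the included antigens", and section 8.2 repeats it almost word for word: "Group B4 is will be compared to groups B1-B3 to show if priming with additional HIV-related plasmids will increase immunogenicity". Neither says whether B1-B3 are pooled or taken one at a time, and neither gives B2 a leading role.

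The arm table in section 1.2 sets out how the groups differ:

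| Group | Plasmids | Electroporation at priming | Boost, weeks 36 and 60 |
|---|---|---|---|
| B1 | 7 | none | MVA |
| B2 | 7 | yes | MVA |
| B3 | 7 | yes | DNA with electroporation |
| B4 | 11, mixed | yes | MVA |

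The table enters B1 as "No electroporation" and the B3 boost as "tot. 0,6 mg DNA + electroporation". Section 2.4.2 agrees: "subjects randomized to Groups B2, B3 and B4 will receive intradermal electroporation over the injection sites".

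Section 8.2 puts the main ELISpot readings two weeks after the third DNA dose and two weeks after each boost, that is, at weeks 14, 38 and 62. It plans significance tests on both the number of responders and the magnitude of response.

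**The concern.** A contrast meant to show what extra plasmids do should hold delivery and boost constant. B4 v B1 changes electroporation as well as plasmids. From week 36, B4 v B3 changes the boost as well. The same list in section 8.2 treats these as separate factors: B2 v B1 is there to isolate electroporation, and B3 v B2 to isolate the boost. The fourth comparison then spans both differences and ascribes the result to plasmids.

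The bias runs in the direction the trial hopes to see, because the Introduction expects electroporation to raise responses. If it does, B4 can look better than the B1-B3 pool, or better than B1 alone, with no contribution from the four added plasmids. Section 8.1 says these comparisons are to shape the hypothesis for a planned trial in Tanzania, so a misattributed difference could mislead that step.

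**Working it through.** **Checking the design reading.** The arm table gives 4 x 10 = 40 exposed to HIV DNA, 3 x 10 = 30 exposed to MVA (B1, B2, B4) and 3 x 12 = 36 exposed to electroporation (B2, B3, B4 with placebo). These are the 40, 30 and 36 of section 8.1, so the reading of the arms is right. The protocol states no power or effect size for the B4 comparison.

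**Inputs.**
- Ten vaccinees per arm (section 1.2).
- B1 at week 14: 30%, from the 3/10 that the Introduction reports for intradermal DNA priming alone. This is an assumption. That regimen used five injections and 1.0 mg; B1 uses two injections and 0.6 mg.
- Electroporated arms at week 14: 70, 80, 90 or 100%. Assumed range.
- MVA-boosted arms after the boosts: 92%, from the 34/37 in the Introduction. Assumed to carry over, and equal in B1, B2 and B4.
- B3 after the boosts: 50% or 30%. Assumed.
- No plasmid effect; Fisher's exact test, two-sided 5%. The test and level are assumptions, since the protocol names neither.

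**Week 14, pooled.** With a common rate e in the electroporated arms, the pooled rate is (0.30 + 2e)/3 and the spurious difference is e - (0.30 + 2e)/3 = (e - 0.30)/3. At e = 0.80 the pool is 1.90/3 = 63.3%, so the difference is 16.7 points. Rejection probabilities come from exact binomial enumeration.

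| e | Spurious difference | B4 v pool (10 v 30) | B4 v B1 (10 v 10) | B4 v B2 (10 v 10) | B4 v B2+B3 (10 v 20) |
|---|---|---|---|---|---|
| 70% | +13 points | 6% | 24% | 1.2% | 3.1% |
| 80% | +17 points | 10% | 43% | 0.8% | 2.2% |
| 90% | +20 points | 14% | 67% | 0.1% | 1.3% |
| 100% | +23 points | 3% | 95% | 0% | 0% |

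For magnitude on the log scale, one third of any electroporation effect enters the pooled contrast. A 3-fold effect would appear as 3^(1/3) = 1.44-fold.

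**After the boosts.** The pooled rate is (2 x 0.92 + x)/3, where x is the B3 rate.

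| B3 | Spurious difference, pooled | B4 v pool | B4 v B3 | B4 v B2 |
|---|---|---|---|---|
| 50% | 92 - 78 = +14 points | 3% | 34% | 0.1% or less |
| 30% | 92 - 71.3 = +21 points | 14% | 72% | 0.1% or less |

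If B3 responded at 78%, B4 v B3 would reject in only 2%.

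**What the matched contrast still mixes.** B4 receives all plasmids mixed in both arms, whereas B2 receives the two ampoules separately. If plasmids are present in equal mass, which the protocol does not state, the amount per plasmid and visit is 0.6/11 = 0.055 mg in B4. In B2 it is 0.3/4 = 0.075 mg for env and rev, and 0.3/3 = 0.10 mg for gag and RT.

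**The case against.** The text does not call for pooling, and B2 lies inside B1-B3. The neighbouring comparisons in section 8.2 let an alert reader see what separates B4 from B1 and B3, all participants' results are to be tabulated, and section 7.7.4 promises an analysis plan before the code is broken. All of that stands. So a reader might infer that an electroporation or MVA effect will be reported as a plasmid effect, and the documents do not support that certainty: taken arm by arm, B4 v B2 would sit beside the other contrasts and, with no plasmid effect, reject in about 1% of trials or fewer.

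A reader might also infer that the whole of objective 5 is compromised. It is not. Nef and tat are in neither the seven plasmids nor the MVA as described, so electroporation or MVA in the comparator arms can hardly imitate a response to them. The problem lies with shared or cross-reactive antigens, which the planned wording includes by covering any included antigen.

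Finally, this is a secondary comparison in a phase I trial that section 8.1 calls descriptive, and no decision rule ties the eleven-plasmid product to it. That lowers the weight. It does not make B1, or B3 after week 36, a proper comparator for a plasmid effect, and section 8.2 does plan significance tests.

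**Conclusion.** The point holds. As worded, sections 1.5.2 and 8.2 name a comparator group in which one arm lacks electroporation throughout and another lacks MVA from week 36. An effect of either can therefore be read as a plasmid effect on shared antigens. The MVA part applies only to weeks 38 and 62; at week 14, B3 has had the same regimen as B2.

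Under the pooled reading the harm is mainly a biased estimate, since rejection rates stay modest. The high rejection rates belong to B4 v B1 and to B4 v B3 after the boosts. All of these sizes depend on assumed response rates; that the contrast is confounded follows from the arm table alone.

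A reader might take B4 v B2 for a clean estimate of the plasmid effect. The documents do not support that either. The synopsis has B4 recruited separately, and section 2.4 gives it its own randomisation list, so the contrast is non-randomised; it also combines plasmid number with mixing of ampoules and possibly less DNA per plasmid. Should fix, not must-fix.

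**What to change.** In sections 1.5.2 and 8.2, replace B1-B3 as the comparator for B4 with B2 at weeks 38 and 62, and with B2 and B3 combined at week 14. Present B1, and B3 after week 36, descriptively only for this question. Add a sentence saying that the comparison of B4 with its matched arms is non-randomised and concerns plasmid number together with mixing of ampoules and any resulting change in DNA per plasmid, so that a difference cannot be assigned to the extra plasmids alone.

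The change is to wording only; arms, visits and sample size stay as they are. The price is a comparator of 20 vaccinees at week 14 and 10 at weeks 38 and 62, instead of 30, and hence wider intervals.

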### 9 Confidentiality, ethics and responsibilities, including indemnity

Full medical confidentiality will be preserved.

The study will be conducted according to ICH GCP guidelines and the Declaration of Helsinki (version 2008), and is the responsibility of the Clinical Investigators.

The Sponsor has delegated the following responsibilities as outlined below.

The Principal and Clinical Investigators are responsible for obtaining the appropriate Regional Ethics Committee approval for the study protocol, the subject information sheet and the consent form. The Principal and Clinical Investigators are responsible for informing the ethics committee of any SAEs as required, and submitting annual reports as required.

Regulatory submissions will be made in Sweden, in collaboration with [name] and a regulatory consultant. [name] will take responsibility for providing required documentation for the HIV DNA vaccines, the Walter Reed Army Institute of Research for the HIV MVA vaccine. Regulatory approval must be provided before study materials will be shipped to the clinical centre. Vecura will be responsible for supply and labelling of the DNA.

The SC will be responsible for assigning an independent statistician to prepare the randomisation list, all aspects of data management including preparing for study-independent monitoring of the clinical sites, and the analysis. Staff will also be responsible for coordinating the response to any SAEs that arise during the course of the trial and reporting these if indicated to the regulatory authorities.

The Swedish Institute for Infectious Disease Control will act as Sponsor for the trial, and will coordinate the necessary clinical trial agreements delineating the above responsibilities and the liability for events occurring as a result of participating in the trial. These agreements must be signed by all parties involved before materials are shipped to the relevant clinical centre. Indemnity will be ensured by the following parties:

- The Principal Investigators will ensure that all clinical staff engaged in the study are covered for negligent harm to a participant, either through a personal or hospital insurance scheme
- Vecura will ensure that a policy providing similar assurance for the DNA vectors is in place. The pharmaceutical insurance will indemnify those suffering adverse events of insured pharmaceuticals if the injury with proponent probability has been caused by a pharmaceutical.
- The Swedish Institute for Infectious Disease Control will be responsible as Sponsor for ensuring that a policy is in place to cover ‘no fault compensation’ for participants on the trial who suffer an adverse event that is attributable to participation in the trial but which is not related to product or due to negligent harm caused by the clinical staff.

Volunteers, as well as patients, in clinical trials performed in the health care settings and approved by an ethics committee are by Swedish law indemnified for damage due to negligent harm caused by the clinical staff.

# 10 Protocol amendments

The protocol team prepares any amendments needed for approval of the HIVIS steering committee. Amendments to the protocol will be made only after consultation and agreement between sponsors and investigator. The only exception is where the investigator considers that a subject’s safety is compromised without immediate action. All amendments that have an impact on subject risk or the study objectives, or require revision of the informed consent document, must receive approval from the Medical Products Agency (Läkemedelsverket) and the ethical committee prior to their implementation. Relevant information in the investigators brochure (IB, prövarhandbok) and participant information (deltagarinformation) will be updated in the event of submission of an amendment to the protocol and submitted to MPA.

**11 Publication**

It is intended that the results of this study will be published in an appropriate peer-reviewed journal, with the aim of submitting a paper for publication within 6 months of the study’s completion. The HIVIS Steering Committee and the HIVIS Trial Coordinating Committee including Bioject Inc and Cyto Pulse Sciences Inc will have 30 days to comment on any manuscript. No other publications, whether in writing or verbally, will be made before the definitive manuscript or abstract for a scientific meeting has been agreed and accepted for publication, without the prior approval of these committees.

A final report of the study will be prepared by the investigators and circulated to the HIVIS Steering Committee for comments.

